## Abstract

**Background:**

Studies have demonstrated that, for patients with psychosis, a majority of the decline in health status and functioning emerges during the first few years after the onset of illness. This knowledge led to the development of specialized early intervention services (EISs) targeting patients experiencing their first episode of psychosis. The central component of EISs is often assertive case management delivered by a multidisciplinary team, where an appointed key worker is responsible for coordinating treatment and delivering various psychosocial interventions to service users.

**Objective:**

This paper outlines the protocol for a feasibility study examining how key workers may enhance physical health by supporting integration between primary and secondary care.

**Methods:**

Semistructured interviews were conducted with key stakeholder groups (General Practitioners and health care professionals working in mental health services). The interviews informed the development of the complex intervention involving a longitudinal pre-post intervention in 8 general practices in 2 regions in Ireland (one urban and one rural). Patients with first episode psychosis (FEP) will be identified from clinical records at general practices and mental health services.

**Results:**

Baseline and follow-up data (at 6 months) will be collected, examining measures of feasibility, acceptability, and intervention effect size.

**Conclusions:**

Study findings will inform future practice by examining feasibility of key workers enhancing physical health through improved interaction between primary and secondary care. By identifying issues involved in enhancing recruitment and retention, as well as the likely effect size, the study will inform a future definitive intervention.

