It has been widely documented that individuals living with psychotic-spectrum disorders have high mortality rates [8,9], and patients with severe mental health disorders, such as psychosis, have a life expectancy that is 10 to 25 years lower than age-matched peers in the general population [8,10-16]. This is partly due to higher rates of suicide, which has been found to be up to 12 times greater in this group than the general population [17,18]. However, suicide accounts for only a fraction of this reduced life expectancy, and the majority is due to the higher rates of cardiovascular, pulmonary, and infectious diseases found in this population [17,19]. There is now clear evidence that weight gain, cardiovascular risk, and metabolic disturbance commonly appear early in the course of emerging psychosis and are potentially modifiable [20]. Psychosis is associated with unhealthy lifestyle choices such as high rates of alcohol, drug and tobacco use, poor nutrition, and low activity levels [21-28]. Heavy smoking is 2 to 6 times more common among people with schizophrenia. Obesity exists in 45% to 55% of people with schizophrenia, diabetes in 10% to 15%, and hypertension in 19% to 58% [29-31]. Individuals with severe mental illness receive poorer medical care for their physical health problems than do members of the general population [11,32]. These factors result in poorer health outcomes and mortality in people with psychosis [33,34].

In the Early Intervention in Psychosis (EIP) model of care, First Episode Psychosis (FEP) is defined as “psychotic symptoms that have lasted at least a week (ie, hallucinations and/or delusions with/without evidence of thought disorder for at least seven consecutive days) leading to distress or disruption to functioning” [35] and that continues throughout the entire critical period [36]. The critical period is defined as the first 5 years for a subset of people [35]. For all others, there is international consensus that treatment should continue for at least 2 years [37].

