### Objective

This study aims to inform health policy in Ireland and internationally by conducting a mixed-methods study examining how key workers might enhance integration between primary and secondary care to improve outcomes for patients with FEP. Outcomes of interest include general and mental health outcomes, substance use disorders, and chronic illness and multimorbidity prevalence. We will examine the feasibility, acceptability, and likely efficacy of a key worker–led intervention in a *real-world* clinical setting, thereby informing future definitive interventions in the area.

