### Study Design and Setting

A longitudinal pre-post intervention in 8 general practices in 2 regions in Ireland (one urban and one rural), in which patients with FEP, will be identified from clinical records in general practice (using a previously developed software tool [71]) and in mental health services. Baseline and follow-up data (at 6 months) will be collected on a number of measures of patients’ physical and mental health.

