### Sample Size

Semistructured interviews will be conducted with 16 health care professionals working in mental health services (n=16) to inform the *complex intervention*. Although it is difficult to predict the number of participants required to reach data saturation, our previous qualitative work [72,73] has indicated that 12 to 16 verbatim are required.

The goal of this feasibility study is to estimate rates of recruitment, consent, retention and response, methodological procedures, and issues. In addition, estimation of the parameters of likely primary outcome measures would allow the sample size of a definitive trial to be determined. With an average of 2 patients presenting to a GP with an FEP each year [74], that is, 8 per 4 years, and 8 practices in total across the 2 sites, we consider the sample size will be sufficient to estimate the actual recruitment and retention rates for a sample of patients recruited in primary care and provide data on acceptability of study processes and outcome measures which will inform a future definitive trial.

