## Discussion

### Strengths and Limitations

This study is the first study to examine how key workers might enhance collaboration between primary and secondary care to improve outcomes for patients with FEP. It will provide important information to enhance scientific understanding of the role of key workers in improving health outcomes for patients with FEP. It will provide key information to inform health policy and service development in Ireland and internationally. However, it may be difficult to extrapolate these results among a high-risk population because of the specificity of the symptomatology in the early phases. This study has the potential to make an important impact on patient care and will provide high-quality evidence to help inform health care professionals on the importance of key workers for FEP patients. The intervention is scalable and, therefore, if found to be feasible and acceptable, it can be readily implemented elsewhere and used to guide policy and service development internationally.

Possible limitations of the study include potential issues of bias and lack of generalizability that may arise from the recruitment process, owing to the likelihood that health care professionals who are more interested in research and innovation will choose to participate. As qualitative data analysis is open to interpretation, there are also potential issues of bias that may arise from data analysis. The use of multiple researchers during the qualitative analysis phase will attempt to reduce this possibility. Despite these potential limitations, this study will provide important information regarding the role of key workers in improving collaboration between primary and secondary care to improve health outcomes for patients with FEP.

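### A single-group before-after study cannot supply the intervention effect size or likely efficacy that the protocol promises

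*Protocol article*

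**What the plan says.** Methods, Study Design and Setting, gives the design as "A longitudinal pre-post intervention in 8 general practices in 2 regions in Ireland (one urban and one rural"). The Abstract's Methods paragraph says the same. No comparison group is described anywhere in the article.

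Three places promise an effect of the intervention:

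- Abstract, Results: data at baseline and follow-up will be collected, "examining measures of feasibility, acceptability, and intervention effect size".
- Abstract, Conclusions: "as well as the likely effect size, the study will inform a future definitive intervention".
- Introduction, Objective: "We will examine the feasibility, acceptability, and likely efficacy" of the key worker intervention.

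On how the study will be used, Methods, Sample Size, says that "estimation of the parameters of likely primary outcome measures would allow the sample size of a definitive trial to be determined". The Discussion's Conclusions speak of key parameters for a later randomised trial. Strengths and Limitations says of the intervention that, "if found to be feasible and acceptable, it can be readily implemented elsewhere and used to guide policy and service development internationally". The limitations named there are recruitment bias, limited generalisability and subjectivity in the qualitative analysis. The lack of a comparator is not among them.

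**The concern.** An intervention effect is a contrast with what would have happened to the same patients without the intervention. A single group does not observe that. Its change from baseline adds together any intervention effect, the natural course of illness, the response to usual treatment and regression to the mean.

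The article itself gives reason to expect health to move without the intervention. The Background says that "weight gain, cardiovascular risk, and metabolic disturbance commonly appear early in the course of emerging psychosis", and that most of the decline in health status falls in the first years after onset. It also says that patients early in the illness may respond better to treatment, which could push other outcomes towards improvement. Patients diagnosed in the preceding four years are eligible, so many will be within that period.

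Two things are at stake: what the study may claim at its end, and what number it hands to the definitive trial. A change score labelled as an effect size invites use as a target difference.

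**Working it through.** **The article's own figure.** Two patients per year over 4 years gives 2 × 4 = 8 per practice, and 8 practices give 8 × 8 = 64. This matches the 8 participants per practice in Approach to Sampling and Recruitment. The total of 64 is implied, not printed. The article states no alpha, power, target effect or SD, so there is no power calculation to reproduce. Everything below is illustration with two-sided alpha 0.05 and effects in units of the between-patient SD.

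**Step 1: bias.** Write observed change = true effect + drift, where drift is the change that would occur without the intervention (positive means improvement). One group cannot separate the two terms. The article gives a value for neither.

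**Step 2: consequence if the change becomes the target difference.** Per-arm size at 80% power is n = 2 × (1.96 + 0.8416)² / d² ≈ 15.70 / d². The power actually obtained with true effect δ is about Φ(δ × √(n/2) − 1.96). With an assumed δ of 0.2:

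| Assumed drift (SD) | Apparent effect | n per arm planned | n per arm needed | Actual power |
|---|---|---|---|---|
| −0.1 | 0.1 | 1570 | 393 | above 99% |
| 0 | 0.2 | 393 | 393 | 80% |
| +0.1 | 0.3 | 175 | 393 | 46% |
| +0.2 | 0.4 | 99 | 393 | 29% |

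For the +0.1 row: 0.2 × √(175/2) = 1.87, and 1.87 − 1.96 = −0.09, which gives 46%. Over assumed true effects of 0.1 to 0.3 SD, drift of +0.1 to +0.2 SD leaves power between 15% and 56%. Drift of −0.1 SD inflates the trial or, at a true effect of 0.1, hides the effect entirely.

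**Step 3: precision with no drift at all.** For a mean change standardised by the baseline SD, SE = √[(2(1 − ρ) + d²/2) / n], where ρ is the baseline to follow-up correlation. With n = 64, d = 0.3 and an assumed ρ of 0.5, SE = √(1.045/64) = 0.128, so the 95% CI is 0.3 ± 0.25, or 0.05 to 0.55. With ρ = 0.7 it is 0.10 to 0.50. With 45 completers (an assumed 30% loss) and ρ = 0.5 it is 0.00 to 0.60. These intervals ignore clustering by practice, which would widen them. At the limits 0.05 and 0.55 the Step 2 formula gives 15.70/0.0025 ≈ 6280 and 15.70/0.3025 ≈ 52 per arm. Even an unbiased estimate of this precision could not size a trial.

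**Step 4: would a control group in this study solve it?** Randomising the same 64 patients, 32 per arm, would remove the drift, but the 95% CI half-width would be 1.96 × √(2/32) = 0.49 SD. With an assumed intraclass correlation of 0.05 and 8 per practice, the design effect is 1 + 7 × 0.05 = 1.35 and the half-width is 0.49 × √1.35 = 0.57 SD. The remedy therefore lies in the claims, not in redesigning the study.

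**The case against.** The strongest reply is that the operative sections are more modest than the Abstract. Data Analysis lists only descriptive statistics on recruitment, retention and prevalence, with no efficacy test or success threshold. Sample Size sets the goal as estimating recruitment, consent, retention and response, and speaks of outcome parameters. Those can mean SDs and rates, which a single group can supply. The article already names a definitive or randomised trial as the next step, and the implementation remark is conditional. This stands, and it limits the point in four ways.

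- A reader might infer that the definitive trial will be mis-sized. The article nowhere says that the before-after change will be its target difference. The risk is conditional, though the Abstract's Conclusions invite it by naming the effect size.
- A reader might infer a known direction of bias, such as worsening that hides a benefit or improvement that favours rollout. The Background gives no trend for this cohort over the follow-up period. Its cardiometabolic statement also does not cover the mental health, substance use and general health measures.
- The drift, true effect, correlation and completion figures above are assumptions. Had the change been standardised by its own SD, it would share a scale with the per-arm sizes only at a correlation of 0.5. Step 3 uses the baseline SD for this reason.
- A reader might infer that rollout is planned on this study alone. The text is a remark on scalability, not a plan.

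The reply does not remove the core point. A stated objective and two statements in the Abstract promise quantities that this design cannot produce. Condensation for a journal does not explain that, because a fuller protocol or analysis plan for the same design could not produce them either.

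**Conclusion.** The point holds as a mismatch between design and stated aims. The uncontrolled design is adequate for recruitment, retention, acceptability and outcome SDs. It cannot give an intervention effect size or likely efficacy, and the limitations do not say so. The size of the error cannot be computed from the article. The illustrations show only that assumed drifts of 0.1 SD either way would move the planned trial from 393 per arm to 175 or about 1570, and that sampling error alone spans about 0.05 to 0.55 around an observed 0.3. This should be fixed, but it does not undermine the feasibility aims.

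**What to change.** - In the Abstract (Results and Conclusions) and in the Objective, replace the effect-size and efficacy terms by *within-patient change with 95% CI, not interpreted as an intervention effect*.
- In Sample Size and in the Discussion's Conclusions, state that the parameters taken forward are the outcome SD, the baseline to follow-up correlation, and the recruitment, retention and response rates. State also that the definitive trial's target difference will be justified independently of the before-after change, for example by a minimum important difference.
- In Strengths and Limitations, list the missing comparator and make the implementation and policy statement conditional on a controlled trial.

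The cost is wording only. Recruitment, data collection and care are unchanged, and the claims become more modest.

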**International Registered Report Identifier (IRRID):**

DERR1-10.2196/13115

## Introduction

### Background

Psychosis is a clinical syndrome that affects several domains, including affective, cognitive, motivational, sensory, and social functioning. Psychosis can manifest in a variety of symptoms including positive symptoms (eg, delusions and hallucinations), negative symptoms (eg, reductions in motivation, volition, and emotion experience or expression), declines in cognitive and social functioning, and disorganized speech and behavior [1]. Psychosis often manifests as a symptom of psychotic-spectrum disorders, which include schizophrenia-spectrum disorders (eg, schizophrenia and schizoaffective disorder) and affective disorders with psychotic features (eg, bipolar disorder with psychotic features) [2]. Psychotic-spectrum disorders are associated with severe difficulties in psychiatric, physical, and functional well-being. Each year it is estimated that 1500 people develop a first episode of psychosis in Ireland. The implications of this issue for population health are considerable. Psychosis usually develops in late adolescence or early adulthood, a critical phase of our life cycle in terms of personal, academic, and economic development. In addition, the personal, familial, and societal costs of psychosis are considerable [3-7].

It has been widely documented that individuals living with psychotic-spectrum disorders have high mortality rates [8,9], and patients with severe mental health disorders, such as psychosis, have a life expectancy that is 10 to 25 years lower than age-matched peers in the general population [8,10-16]. This is partly due to higher rates of suicide, which has been found to be up to 12 times greater in this group than the general population [17,18]. However, suicide accounts for only a fraction of this reduced life expectancy, and the majority is due to the higher rates of cardiovascular, pulmonary, and infectious diseases found in this population [17,19]. There is now clear evidence that weight gain, cardiovascular risk, and metabolic disturbance commonly appear early in the course of emerging psychosis and are potentially modifiable [20]. Psychosis is associated with unhealthy lifestyle choices such as high rates of alcohol, drug and tobacco use, poor nutrition, and low activity levels [21-28]. Heavy smoking is 2 to 6 times more common among people with schizophrenia. Obesity exists in 45% to 55% of people with schizophrenia, diabetes in 10% to 15%, and hypertension in 19% to 58% [29-31]. Individuals with severe mental illness receive poorer medical care for their physical health problems than do members of the general population [11,32]. These factors result in poorer health outcomes and mortality in people with psychosis [33,34].

In the Early Intervention in Psychosis (EIP) model of care, First Episode Psychosis (FEP) is defined as “psychotic symptoms that have lasted at least a week (ie, hallucinations and/or delusions with/without evidence of thought disorder for at least seven consecutive days) leading to distress or disruption to functioning” [35] and that continues throughout the entire critical period [36]. The critical period is defined as the first 5 years for a subset of people [35]. For all others, there is international consensus that treatment should continue for at least 2 years [37].

The first few years of psychotic-spectrum disorders are likely to be a *critical period* in which the provision of targeted, phase-specific intervention could dramatically improve the usual course of psychotic-spectrum disorders [38]. Research has demonstrated that a majority of the decline in health status occurs in the first few years following the onset of psychosis [39]. Furthermore, individuals earlier in the course of a psychotic disorder may be more responsive to both pharmacological and psychosocial treatments than those with a more long-standing illness.

In recent years, an international consensus has identified that most people who develop psychosis are unwell for a considerable period of time before seeking help [4,32,40,41]. This time period is called the *duration of untreated psychosis* and it is crucial because the longer individuals with psychosis remain undiagnosed and untreated, the greater the opportunity for adverse physical, psychological, and social outcomes. Reducing the duration of untreated psychosis and ensuring people receive treatment that is specific to the early phase of the illness are associated with improved physical and social outcomes. Therefore, early detection and optimal early treatment in people experiencing their first episode of psychosis have been emphasized as a best practice in FEP literature in recent years [42]. Pioneering work in Melbourne that established *Early Intervention* teams to work with individuals during a first episode of psychosis demonstrated considerable benefits in terms of health gain and satisfaction to the family and economically to the state [43-45] and this model of care has been replicated worldwide [46-48]. These services are characterized by holistic, multimodal, and phase-specific treatment of patients with FEP, typically centred around assertive case management with access to a comprehensive range of pharmacological and psychosocial interventions [49].

Primary care has a key role in the care of patients who experience FEP, and effective links between secondary and primary care have been a key feature of Ireland’s FEP Early Intervention Services (EISs) [50,51]. EISs seek to enhance the outcome trajectories of psychotic-spectrum disorders [38,52,53] by focusing on early detection of new cases [54,55], shortening delays to effective treatment [54,56-58] and providing comprehensive and timely treatment to patients with FEP throughout the entire critical period [58,59]. Early intervention programs generally engage in some form of assertive community treatment [60-62], which attempts to treat patients in the community instead of making use of inpatient services [63]. Therefore, the presence of a primary care point of contact between service users and mental health services is an important factor for many EISs. Key workers have been identified as a key strategy to support patient engagement with mental health services and this is especially the case for patients with psychosis [64,65]. Furthermore, Ireland’s Health Services Executive, specifically the Clinical Programme (Early Intervention for First Episode Psychosis [EIP]) has identified EIP key workers as a key mechanism to enhance links between primary and secondary care and to improve physical health (Early Intervention Services for Psychosis, Submission to the National Clinical Programme HSE by Early Intervention Working Group of the College of Psychiatrists of Ireland, 2015).

Key workers can be from a range of mental health clinical backgrounds but need to be of a certain level of seniority. They must also be adequately trained and maintain competencies in early intervention, skills including assessment of psychosis, relapse prevention, and family psychoeducation and assessment of suicide or violence risk [66]. Key workers can serve as the consistent point of contact between the service user (and family or carers), the EISs, and other agencies involved, provide basic psychosocial interventions, and ensure the organization of individual care plans and service transfers for their patients. EIP key workers have an important role in enhancing initial diagnosis and subsequent treatment for FEP. Increased liaison between primary and secondary care improves the clinical effectiveness and cost-effectiveness of detection of people with or at high risk of developing FEP [67]. Although EISs provide formal structured professional support for service users, the role of EIP key workers from *assessment and engagement* through to the *long-term successful delivery of effective treatments* is also crucial [68]. There is increasing consensus that EIP key workers for those suffering from psychosis are seen as important health care *resources* [69]. With a general consensus that integrated approaches to health care are likely to enhance outcomes, and in the case of patients experiencing FEP, a recognition of the potential of EIP key workers to promote this goal, this is an ideal context in which to examine how EIP key workers can enhance the capacity of primary and secondary care to collaborate to enhance physical health outcomes for people who experience an FEP. This question has not been addressed internationally and such knowledge is needed to inform service development, and especially integrated care, thus reducing the global burden of chronic disease among people with severe enduring mental illness.

